## Abstract

**Background:**

In patients with stable coronary artery disease (CAD), revascularisation decisions are based mainly on the visual grading of the severity of coronary stenosis on invasive coronary angiography (ICA). However, invasive fractional flow reserve (FFR) is the current standard to determine the haemodynamic significance of coronary stenosis. Non-invasive and less-invasive imaging techniques such as computed-tomography-derived FFR (FFR-CT) and angiography-derived FFR (QFR) combine both anatomical and functional information in complex algorithms to calculate FFR.

**Trial design:**

The iCORONARY trial is a prospective, multicentre, non-inferiority randomised controlled trial (RCT) with a blinded endpoint evaluation. It investigates the costs, effects and outcomes of different diagnostic strategies to evaluate the presence of CAD and the need for revascularisation in patients with stable angina pectoris who undergo coronary computed tomography angiography. Those with a Coronary Artery Disease—Reporting and Data System (CAD-RADS) score between 0–2 and 5 will be included in a prospective registry, whereas patients with CAD-RADS 3 or 4A will be enrolled in the RCT. The RCT consists of three randomised groups: (1) FFR-CT-guided strategy, (2) QFR-guided strategy or (3) standard of care including ICA and invasive pressure measurements for all intermediate stenoses. The primary endpoint will be the occurrence of major adverse cardiac events (death, myocardial infarction and repeat revascularisation) at 1 year. Clinicaltrials.gov-identifier: NCT04939207.

**Conclusion:**

The iCORONARY trial will assess whether a strategy of FFR-CT or QFR is non-inferior to invasive angiography to guide the need for revascularisation in patients with stable CAD. Non-inferiority to the standard of care implies that these techniques are attractive, less-invasive alternatives to current diagnostic pathways.

## Introduction and rationale

Invasive coronary angiography (ICA) and invasive pressure measurements such as fractional flow reserve (FFR) are used as the reference standard for the diagnosis of the haemodynamic significance of coronary stenosis. Both ICA and invasive pressure measurements are considered low-risk invasive procedures. If complications occur, these are generally mild, such as bleeding or haematoma at the access location, which happens in approximately 5% of the patients. More serious complications as compartment syndrome, dissection of vessels, myocardial infarction, stroke and cardiac arrhythmias including ventricular fibrillation are rare. Event rates vary between approximately 1/1000 and 1/100,000 procedures, but since ICA and invasive pressure measurements are frequently performed, absolute numbers of serious complications are significant [1]. Besides the additional risks, invasive pressure measurements are an expensive strategy with costs amounting to €1000 per patient in the Netherlands (excluding the costs of catheterisation) [2].

ICA and invasive pressure measurements are not useful if revascularisation is not feasible and expected. Although the rates vary per hospital, approximately 50% of all patients currently referred for invasive tests in the Netherlands do not have a significant lesion, and do not need revascularisation [2]. While clinical evaluation, non-invasive imaging and stress testing are needed for risk stratification in patients with suspected coronary artery disease (CAD), diagnostic over-testing needs to be avoided. The lack of consensus in the current guidelines about the optimal diagnostic pathway for patients with suspected CAD results in major differences in strategies between hospitals. A budget impact analysis performed by the Dutch National Healthcare Institute shows a potential decrease in costs of €177 million per year with improvements in the diagnostic strategy for stable CAD. In addition, favourable effects on the health of patients are expected because of averted side-effects of unnecessary invasive testing [2]. Non-invasive imaging techniques improve the diagnostic process, but the exposure to radiation and/or contrast agent can lead to complications, which increase costs and negatively affect the quality of life. Moreover, most of the diagnostic tests focus either on anatomical or functional information.

New non-invasive and less-invasive imaging techniques, for example computed-tomography-derived FFR (FFR-CT) and angiography-derived FFR [quantitative flow ratio (QFR)], combine both anatomical and functional information. The PLATFORM and FORECAST studies showed conflicting results regarding differences in costs between an FFR-CT-guided strategy and usual care and no differences in clinical outcomes, but the use of ICA decreased [3]. Both FFR-CT and QFR are expected to be cheaper than invasive pressure measurements. Costs amount to approximately €1000 per patient for FFR-CT [excluding the costs for coronary computed tomography angiography (CCTA)] and approximately €500 for QFR (excluding the costs for ICA). We hypothesise that FFR-CT and QFR are more cost-effective in the Dutch healthcare system in comparison to invasive pressure measurements by lowering the percentage of patients referred for invasive pressure measurements. FFR-CT also increases patient comfort and could lead to a lower rate of complications, which adds to its cost-effectiveness. However, evidence is conflicting or lacking and requires more head-to-head cost-effectiveness studies of alternatives to invasive pressure measurements.

The aim of the iCORONARY trial is to determine whether non-invasive or minimal-invasive imaging techniques such as FFR-CT and QFR are a cost-effective and safe alternative to invasive pressure measurements when deciding on the indication for revascularisation in patients with suspected CAD in terms of subsequent major adverse cardiac events (MACE).

## Methods

### Trial design

This study is a prospective, multicentre, non-inferiority randomised controlled trial (RCT) with an open, blinded endpoint evaluation (PROBE design) investigating the costs, effects and outcomes of different diagnostic strategies to establish the presence or absence of flow-limiting coronary artery stenoses in need of revascularisation according to the guidelines. The study design is pragmatic and closely follows currently used diagnostic pathways and tests in clinical practice (Fig. 1).

**Fig. 1 Fig1:**
[figure not shown]
Study flow chart. Patients are considered “lost to follow-up” if they retract their informed consent at any point during the study. In this case, data collected so far can still be used. Information regarding death of a subject will be obtained via medical records, the patient’s general practitioner and Statistics Netherlands. *CAD-RADS* Coronary Artery Disease—Reporting and Data System, *CCTA* coronary computed tomography angiography, *FFR* fractional flow reserve, *FFR-CT* computed tomography derived fractional flow reserve, *ICA* invasive coronary angiography, *QFR* quantitative flow ratio

### Patient selection

This study concerns patients referred to a cardiologist with chest pain of suspected coronary origin. Only patients who had no prior coronary interventions are eligible to participate. Detailed inclusion and exclusion criteria are listed in Tab. 1. All eligible patients will undergo CCTA. CCTA images will be assessed using the standardised Coronary Artery Disease—Reporting and Data System (CAD-RADS) [4]. The CAD-RADS score distinguishes patients with absence of CAD (CAD-RADS 0) and mild, non-obstructive stenosis (CAD-RADS 1 and 2) from patients with moderate or higher degrees of stenosis (CAD-RADS 3–5). After giving signed informed consent, participants are recruited based on their CAD-RADS result into either the registry part or the randomised part of the study:Patients with CAD-RADS between 0–2 and 5 are included in a prospective multicentre registry in which we will assess outcomes at 12 months after CCTA. Follow-up of these patients ensures we obtain a “real-world” estimate of the ability of CCTA to adequately triage patients with no or low CAD disease burden from patients with intermediate to severe CAD disease burden as practiced in the Netherlands.Patients with CAD-RADS 3 or 4A in at least one vessel are included in the RCT and randomised to: (1) a usual care arm, (2) an FFR-CT-guided revascularisation arm, and (3) a QFR arm.

**Table 1 Tab1:** Inclusion and exclusion criteria, which are similar for both the registry and the randomised controlled trial (RCT). Patients with a Coronary Artery Disease—Reporting and Data System (CAD-RADS) score of 3 or 4A in at least one vessel are included in the RCT, whereas patients with CAD-RADS 0–2 or 5 are eligible for the registry

Inclusion criteria	Exclusion criteria
The subject is ≥ 18 years of age	The subject is suffering from unstable angina pectoris
The subject is willing and able to provide informed consent and to adhere to study rules and regulations as well as follow-up requirements	The subject is suffering from decompensated congestive cardiac failure
	The subject is suffering from a known non-ischaemic cardiomyopathy
There is a clinical suspicion of (recurrent) angina pectoris or an equivalent symptom and suspected coronary artery disease, based on symptoms and signs, history, clinical examination and baseline diagnostic testing (e.g. ECG recording and laboratory tests) as described in the 2019 ESC guideline on chronic coronary syndromes	The subject has a history of percutaneous coronary intervention or coronary artery bypass grafting
	The subject has had pacemaker or internal defibrillator leads implanted
	The subject has a prosthetic heart valve
	There is a severe language barrier
	The subject is participating in any other clinical trial that interferes with the current study
The subject has had ≥ 64 multidetector row coronary CTA or will undergo coronary CTA as part of usual care deemed necessary by the treating physician with ≥ 64 multidetector row coronary CTA	The subject’s clinical condition prohibits subsequent interventional therapy as indicated by the results of the imaging procedures
	The subject is or might be pregnant
	The subject does not comply or is not able to comply with the imaging guidelines for the performance and acquisition of coronary CTA as defined by the SCCT

*CTA* computed tomography angiography, *ECG* electrocardiogram, *ESC* European Society of Cardiology, *SCCT* Society of Cardiovascular Computed Tomography

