### Primary outcome

The primary clinical outcome for both the registry and the RCT is the occurrence of MACE within 12 months of follow-up. This composite endpoint includes all-cause mortality, aborted sudden cardiac death, myocardial infarction and unplanned hospitalisation for chest pain leading to urgent revascularisation (Tab. 2).

**Table 2 Tab2:** Definitions of primary and secondary endpoints, which are similar for both the registry and the randomised controlled trial

Endpoint	Definition
*Primary endpoint and components*	
Major adverse cardiac events	Composite of all-cause mortality, aborted sudden cardiac death, myocardial infarction and unplanned (acute) hospitalisation leading to urgent revascularisation
All-cause mortality	Death of a subject during the study, defined as 12 months after the inclusion of the final subject, regardless of the cause or circumstances of death
Aborted sudden cardiac death	Successful reversal of unexpected circulatory arrest, with the arrest occurring within 1 h of onset or worsening of acute symptoms, by resuscitation manoeuvres (i.e. chest compressions, cardiac defibrillation), resulting in sustained return of spontaneous circulation or sustained extracorporeal circulatory support for at least 20 min [16, 17]
Myocardial infarction	Acute myocardial infarction type 1–3 and procedure-related myocardial infarction type 4 and 5 as defined by the fourth universal definition of myocardial infarction [18]
Unplanned hospitalisation leading to urgent revascularisation	Unplanned hospitalisation due to chest pain or other symptoms suspected to be caused by myocardial ischaemia, but not meeting the criteria for myocardial infarction as defined by the fourth universal definition of myocardial infarction, resulting in urgent coronary revascularisation
*Secondary endpoints*	
Unstable angina	Defined by the ESC as myocardial ischaemia at rest or on minimal exertion in the absence of acute cardiomyocyte injury/necrosis [19]
Non-fatal stroke	Survival of at least 28 days after the onset of stroke, defined as a focal (or at times global) neurological impairment of sudden onset of presumed vascular origin, lasting more than 24 h (or resolved by treatment but expected to have lasted more than 24 h in the absence of treatment) [20]

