#### Study endpoints and questionnaires

Clinical endpoints, mortality and MACE will be obtained from the electronic patient records and other data sources (general practitioner, national death registry and participants themselves) until the end of the study (at least 12 months’ follow-up for each participant, maximum follow-up 30 months). A blinded clinical endpoint committee will adjudicate all endpoints.

Symptoms of angina are recorded by use of the Seattle Angina Pectoris Questionnaire and mental status is assessed using PHQ‑9. Medical costs and productivity losses are recorded using the iMTA Medical Consumption Questionnaire and iMTA Productivity Cost Questionnaire (iMTA, Rotterdam, The Netherlands). Health-related quality of life, as measured by the Patient-Reported Outcome Measurement Information System (PROMIS-10), including the score on the European Quality of Life 5 Dimensions 5 Levels questionnaire (EQ-5D-5L; EuroQol, Rotterdam, The Netherlands), will be established at baseline and 1, 3, 6 and 12 months after inclusion. In addition, patients will be asked to complete a test rating scale for discomfort and satisfaction with the testing procedure. Patients who receive an invasive pressure measurement after the FFR-CT or QFR test will be asked to compare the tests directly.

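### The registry's 12-month clock starts at the CCTA but patients can enter after it, so time in which death or revascularisation bars entry counts as follow-up and biases the MACE rate downward

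*Protocol article*

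**What the plan says.** Under Patient selection, the protocol article says that patients with CAD-RADS 0–2 or 5 "are included in a prospective multicentre registry in which we will assess outcomes at 12 months after CCTA". That sentence sets the registry's time zero at the scan.

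Entry comes later for some patients. Table 1 accepts a scan already made as well as one still to come: "multidetector row coronary CTA or will undergo coronary CTA as part of usual care deemed necessary by the treating physician". The same section describes the order of steps: "After giving signed informed consent, participants are recruited based on their CAD-RADS result into either the registry part or the randomised part of the study". Table 1 also lists an exclusion: "The subject has a history of percutaneous coronary intervention or coronary artery bypass grafting".

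Other sections use other clocks:

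- Primary outcome: "The primary clinical outcome for both the registry and the RCT is the occurrence of MACE within 12 months of follow-up", with no start of follow-up given.
- Table 2, all-cause mortality: "Death of a subject during the study, defined as 12 months after the inclusion of the final subject".
- Study endpoints and questionnaires: the health-related quality-of-life measures "will be established at baseline and 1, 3, 6 and 12 months after inclusion".

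**The concern.** If the clock starts at the scan and a patient joins only after it, the time in between is follow-up the patient had to survive in order to be counted. This is immortal time. Here it also screens out non-fatal events, because PCI or CABG before entry is an exclusion and urgent revascularisation is itself a component of the primary composite. Some patients would be left out because they had the outcome.

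Twelve-month MACE is the primary outcome of the registry as well as of the RCT, and the Sample size section puts about 75% of the 3300 patients in follow-up only. The registry is meant to give a real-world estimate of how well CCTA triages patients. A rate that can err only downward weakens that estimate.

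**Working it through.** **1. The plan's own figures.** No registry event rate, precision target or scan-to-consent lag is stated, so there is no registry figure to reproduce. The one sample-size figure that can be recomputed is the RCT's 221 per arm: (1.96 + 0.84)² × 2 × 0.037 × 0.963 / 0.05² ≈ 224, within 1.4% of 221. It does not depend on the registry clock and is unaffected.

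**2. Which early events are lost.** Take an event between CCTA and consent and apply the stated entry rules.

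| Event before consent | Can the patient still enter? |
|---|---|
| Death | No, consent is impossible |
| Urgent revascularisation | No, PCI/CABG is an exclusion |
| Infarction treated by, or caused by, PCI/CABG | No, same exclusion |
| Infarction or aborted sudden death without revascularisation | Yes, not a listed exclusion |

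The interval is therefore partly, not wholly, cleared of events.

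**3. Size.** Let p be the true 12-month risk after CCTA, with constant hazard λ = −ln(1 − p)/12 per month. Suppose every patient enters L months after the scan and every event in that interval bars entry. The risk seen at 12 months after CCTA is then 1 − exp(−λ(12 − L)), a relative shortfall of about L/12. The values of p and L are assumptions. 3.7% is the RCT's control-arm rate, used only as an illustration, and 1% is a lower value. The registry is taken as 0.75 × 3300 = 2475 patients.

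| Lag L | Seen if p = 1% | Seen if p = 3.7% | Relative shortfall | Events seen, p = 1% (true 24.8) | Events seen, p = 3.7% (true 91.6) |
|---|---|---|---|---|---|
| 0.5 month | 0.96% | 3.55% | 4% | 23.7 | 87.8 |
| 1 month | 0.92% | 3.40% | 8% | 22.7 | 84.1 |
| 3 months | 0.75% | 2.79% | 25% | 18.6 | 69.0 |

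Under a constant hazard these are upper bounds. The shortfall shrinks with the share of patients who entered after the scan and with the share of early events that bar entry. If half the patients had a 1-month lag, for example, it is about 0.5 × 8% = 4%.

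**4. Contrast between CAD-RADS groups.** With a common 3-month lag, groups at 1% and 3.7% would show 0.75% and 2.79%. The ratio stays at 3.7 (2.79/0.75), while the absolute difference falls from 2.7 to about 2.0 percentage points (2.79 − 0.75).

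**5. The clocks side by side.** Registry outcomes run from CCTA, the primary outcome has no stated start, deaths run to a calendar date set by the last inclusion, and questionnaires run from inclusion. These coincide only if CCTA and inclusion fall together, and even then not for deaths, since maximum follow-up is 30 months. They must be reconciled whatever the lag turns out to be.

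**The case against.** The strongest reply is that the CCTA phrase is one descriptive clause. The section defining the primary outcome does not use it. Study endpoints and questionnaires promises at least 12 months' follow-up per participant, and the time-line section speaks of patients included and then followed for 12 months. If follow-up really runs from inclusion, the clock causes no bias. The article also says "All eligible patients will undergo CCTA", which suggests current scans, and patients who consent before or around the scan contribute no bias. This lowers the likely size, but the CCTA clock is still the only explicit start given for registry outcomes, and Table 1 expressly allows entry after the scan.

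A reader might infer four stronger points that the document does not support:

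- **Scans of any age are allowed.** This is read from silence. The article condenses a full protocol that may set a limit, so a missing limit is not a finding.
- **The whole interval is event-free.** Infarction or aborted sudden death without revascularisation does not bar entry, and a planned revascularisation before consent removes a patient without losing a MACE.
- **CAD-RADS 5 is hit hardest because its events come early.** If half the 12-month hazard fell in the first 3 months, a 3-month lag would lose about 50%, but nothing in the document supports that pattern.
- **The FFR-CT arm is handicapped.** Any scan-to-randomisation lag precedes allocation, so it does not bias the comparison between arms. The sentence at issue concerns the registry only.

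**Conclusion.** The point holds for the registry. As written, a CCTA time zero, entry after a completed CCTA, and exclusion of patients who have died or been revascularised together bias the registry's 12-month MACE rate downward for patients who enter after the scan. The direction follows from the stated rules; the size does not. Under a constant hazard, with all patients lagged and all early events lost, the relative bias is at most about 8% at 1 month and 25% at 3 months, and about 4% at two weeks. Separately, the sections name different clocks and need reconciling. The RCT comparison and its sample size are not affected.

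**What to change.** State one time zero for the registry's primary outcome and use it in Patient selection, Primary outcome and Table 2. Either option works:

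- count 12 months from inclusion, as the questionnaires already do; or
- keep time since CCTA as the scale, with delayed entry (left truncation) at inclusion, so that pre-consent time is not at risk.

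Report the distribution of the CCTA-to-inclusion interval by CAD-RADS group.

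The cost is small: the change needs the CCTA and inclusion dates and no extra follow-up, because each participant is already to be followed for at least 12 months.

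The downside should be stated as a limitation. Either estimate is conditional on being alive and not revascularised at inclusion, and events before consent that bar entry remain unobserved. Counting from inclusion equals the 12-month risk after CCTA only if the hazard is constant, and it moves the estimate away from risk after the scan, which is closer to the triage aim. Delayed entry keeps that scale, but needs enough patients included soon after CCTA and entry times unrelated to later risk.

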### Primary outcome

The primary clinical outcome for both the registry and the RCT is the occurrence of MACE within 12 months of follow-up. This composite endpoint includes all-cause mortality, aborted sudden cardiac death, myocardial infarction and unplanned hospitalisation for chest pain leading to urgent revascularisation (Tab. 2).

**Table 2 Tab2:** Definitions of primary and secondary endpoints, which are similar for both the registry and the randomised controlled trial

Endpoint	Definition
*Primary endpoint and components*	
Major adverse cardiac events	Composite of all-cause mortality, aborted sudden cardiac death, myocardial infarction and unplanned (acute) hospitalisation leading to urgent revascularisation
All-cause mortality	Death of a subject during the study, defined as 12 months after the inclusion of the final subject, regardless of the cause or circumstances of death
Aborted sudden cardiac death	Successful reversal of unexpected circulatory arrest, with the arrest occurring within 1 h of onset or worsening of acute symptoms, by resuscitation manoeuvres (i.e. chest compressions, cardiac defibrillation), resulting in sustained return of spontaneous circulation or sustained extracorporeal circulatory support for at least 20 min [16, 17]
Myocardial infarction	Acute myocardial infarction type 1–3 and procedure-related myocardial infarction type 4 and 5 as defined by the fourth universal definition of myocardial infarction [18]
Unplanned hospitalisation leading to urgent revascularisation	Unplanned hospitalisation due to chest pain or other symptoms suspected to be caused by myocardial ischaemia, but not meeting the criteria for myocardial infarction as defined by the fourth universal definition of myocardial infarction, resulting in urgent coronary revascularisation
*Secondary endpoints*	
Unstable angina	Defined by the ESC as myocardial ischaemia at rest or on minimal exertion in the absence of acute cardiomyocyte injury/necrosis [19]
Non-fatal stroke	Survival of at least 28 days after the onset of stroke, defined as a focal (or at times global) neurological impairment of sudden onset of presumed vascular origin, lasting more than 24 h (or resolved by treatment but expected to have lasted more than 24 h in the absence of treatment) [20]
Avoided ICA procedures	The number of ICA procedures that were not performed due to the availability of FFR-CT, but that would have been indicated based on the results of non-invasive diagnostic tests if FFR-CT had not been available
Avoided FFR measurements	The number of FFR measurements that were not performed due to the availability of QFR, but that would have been indicated based on the anatomical stenosis severity visible on angiographic images if QFR had not been available

*ESC* European Society of Cardiology, *FFR* fractional flow reserve, *FFR-CT* computed tomography derived fractional flow reserve, *ICA* invasive coronary angiography, *QFR* quantitative flow ratio

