#### Sample size

The sample size calculation is based on the expected percentage of patients with the primary composite endpoint of MACE at 12 months. A 3.7% incidence in the FFR-guided arm and a non-inferiority margin of 5% are assumed based on the results of the MR-INFORM trial [11]. With these assumptions, a sample size of 221 patients in each arm is estimated to determine non-inferiority (one-sided level of significance of 0.025) and to provide the trial with at least 80% power. Based on local experience approximately 25% of the patients evaluated by CCTA have a CAD-RADS score of 3 or 4A. The pertinent literature suggests that a maximum of 15% of the patients are not suitable for FFR-CT or QFR analyses [8, 9, 12–14]. Allowing for an exclusion percentage of 15% and a dropout rate caused by loss to follow-up of 5%, a total sample size of 3300 patients is required. It should be noted that 75% of these patients are asked for follow-up only (CAD-RADS 0–2), and 25% (*n* = 825) will be randomised to the different techniques to measure FFR.

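### Table 2 runs the death component of the primary composite to study end, which contradicts the 12-month primary endpoint on which the trial is sized

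*Protocol article*

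**What the plan says.** Three places in the protocol article set the primary endpoint at 12 months:

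- Abstract, Trial design: "The primary endpoint will be the occurrence of major adverse cardiac events (death, myocardial infarction and repeat revascularisation) at 1 year".
- Methods, Primary outcome: "occurrence of MACE within 12 months of follow-up", for both the registry and the RCT.
- Sample size: the calculation uses the "primary composite endpoint of MACE at 12 months", with 3.7% expected, a 5% margin and 221 patients per arm.

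Table 2 defines MACE as "Composite of all-cause mortality, aborted sudden cardiac death, myocardial infarction and unplanned (acute) hospitalisation leading to urgent revascularisation", with no time limit in that row. Under the same block of primary endpoint components, it defines all-cause mortality as "Death of a subject during the study, defined as 12 months after the inclusion of the final subject". No other component in the table has a time window of its own.

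The section Study endpoints and questionnaires has clinical endpoints, mortality and MACE collected until study end, with at least 12 months per participant and "maximum follow-up 30 months". The time line section ends the trial once 3300 patients are included and followed for 12 months.

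**The concern.** The mortality row describes a date that is the same for all patients. The outcome sentence describes a period that starts anew for each patient. The two agree only for the last patient included. A death in month 20 of an early patient is a primary event under the Table 2 row and is not one under the outcome sentence.

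This matters because the trial expects few events: 3.7% of 221 is about 8 per arm. If the row were followed literally, the composite would combine infarction, aborted sudden death and urgent revascularisation over 12 months with deaths over 12 to 30 months. The observed rate would then be set against a planning rate and a margin that were both chosen for 12-month MACE. A choice of window made after the data are seen would also leave a non-inferiority result open to challenge.

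**Working it through.** **1. Reproduce the plan's figure.** Inputs from Sample size: p = 0.037 in both arms, margin 0.05, one-sided α = 0.025, power 80%.

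n = 2p(1−p)(1.960 + 0.842)² / 0.05² = 0.07126 × 7.849 / 0.0025 = 223.7, so 224 per arm against 221 stated.

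Power at 221 = Φ(0.05/√(2 × 0.037 × 0.963/221) − 1.96) = Φ(2.784 − 1.960) = 79.5%.

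Inflation: 3 × 221/(0.85 × 0.95) = 821 against 825 stated, and 825/0.25 = 3300. The stated size therefore fits a true 12-month endpoint.

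**2. Length of the Table 2 window.** Maximum follow-up is 30 months and the minimum is 12, so the row extends up to 30 − 12 = 18 months past the primary window. With uniform accrual over those 18 months (assumed), mean follow-up is (12 + 30)/2 = 21 months, or 9 extra months on average.

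**3. Effect if the row were applied to the composite.** The article gives no death rate, so annual mortality d is assumed. Replacing 12-month deaths by deaths over 21 months gives

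p(d) = 0.037 − d + [1 − (1 − d)^(21/12)].

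Example, d = 1%: 0.037 − 0.010 + 0.0174 = 0.0444. Power at 221 = Φ(2.551 − 1.960) = 72%.

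| Assumed d | Composite | n per arm for 80% | Power at 221 |
|---|---|---|---|
| none added | 3.7% | 224 | 79.5% |
| 0.2% | 3.85% | 233 | 78% |
| 0.5% | 4.1% | 246 | 76% |
| 1.0% | 4.4% | 267 | 72% |
| 2.0% | 5.2% | 309 | 66% |

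**4. Dependence on the number analysed.** The 221 allows for both the 15% exclusion and the 5% dropout. If 825 patients are randomised equally (275 per arm) and only the 5% dropout is removed, 275 × 0.95 ≈ 261 per arm remain. The same formula then gives about 82%, 79% and 73% at d = 0.5%, 1% and 2%, against about 86% with no added deaths.

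**The case against.** The best defence is that the 12-month limit governs. It is stated three times, one of them in the sentence that defines the primary outcome, and the MACE row in Table 2 carries no study-end window. Table 2 serves primary and secondary endpoints alike, the Secondary outcome section makes the individual components secondary outcomes, and mortality is collected to study end. The row may therefore describe death as collected, or as a secondary outcome of its own, with the composite still cut at 12 months. That reading is plausible, and it is why the point is a contradiction to reconcile and not proof that late deaths will be counted. It does not remove the conflict: the row stands under the primary components, no 12-month version of death is given, and nothing says which statement prevails. The Data analyses section does not settle it either. It names Kaplan-Meier curves and the log-rank test without a cut at 12 months, though such detail is commonly left to an analysis plan.

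It is also fair to object that the power loss rests on assumptions. At d = 2%, death would make up 2.0/3.7 = 54% of the assumed 12-month composite, which nothing in the article supports. At d = 0.2% the loss is under 2 points.

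A reader might further infer a conflict over when the clock starts. For the registry the article says "we will assess outcomes at 12 months after CCTA", while visits elsewhere are timed from inclusion. The documents do not support this as a contradiction: the first statement concerns the registry, which studies triage by CCTA, and the second schedules the quality-of-life questionnaires.

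**Conclusion.** The mortality row in Table 2 is wrong as written, because it contradicts the 12-month primary endpoint given in the abstract, the outcome sentence and the sample size section. This holds whatever the death rate.

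The consequence is conditional. Only if the row is applied to the composite does the event rate exceed the 3.7% planned. Under uniform accrual over 18 months and annual mortality of 0.2% to 2%, both assumed, the composite would be about 3.9% to 5.2%. Power at 221 per arm would be about 78% to 66% instead of 79.5%, with higher values if more of the 825 are analysed.

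A reader might go further and conclude that the composite is not a 12-month endpoint, or that the stated power no longer applies. The article does not support either as a flat statement, since the planning used 12-month MACE and reproduces on that basis. Nor does bias between arms follow: randomisation should balance length of follow-up.

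**What to change.** In Table 2, define all-cause mortality for the primary composite as death within 12 months of randomisation for RCT patients, and within 12 months of the registry's own stated origin for registry patients. State that the primary analysis is censored at 12 months. Report deaths to study end as a separate secondary outcome.

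The cost is one row in the endpoint table and one sentence in the analysis section, settled before the outcome data are examined. Later deaths are still collected and reported, so no data are lost. The sample size needs no change for this, because it was already calculated for a 12-month endpoint.
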